### Blind reading of outcomes

The information of patients in our study will be accessible to the surgeon responsible for numbering and including patients, the investigator managing synovial fluid samples and the investigator collecting the test results. The results of objective indicators, including demographic characteristics, serum CRP, serum IL-6, serum D-Dimer, ESR, culture results (tissue or synovial fluid), drug sensitivity, histological analysis, synovial white blood cell (WBC) counts and synovial polymorphonuclear neutrophil percentage (PMN%), will be directly recorded by the investigator collecting test results.

The remaining indicators will be first processed and evaluated by an investigator blinded to the details of the patients and samples. Changes on the leukocyte esterase (LE) test strips will be evaluated by an investigator without knowledge of patient information. Synovial alpha-defensin and synovial CRP will be measured by an investigator who obtains only the samples and sample numbers. However, the presence of purulence will be determined by the surgeons who are in control of patient information. These processed data will be collected by the investigator who subsequently collects the test results.

The investigator responsible for statistical analysis will also be blinded to patient information. Nevertheless, it is impossible for the surgeons and resident physicians who extract synovial fluid to be blinded.

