## Methods

### Study design and objectives

This single-centre trial is designed as a prospective diagnostic study. The objectives of this study are to supplement and improve the results of the preceding prospective study and to validate the feasibility of the 2018 new PJI definition for Chinese patients. The study is nonrandomized, and all patients serve as their own controls. From October 2019 to October 2020, we will recruit patients who agree to participate in the trial in the Department of Orthopaedics of the Chinese PLA General Hospital (301 hospital). Blood samples, synovial fluid samples and intraoperative findings will be collected for patients meeting the inclusion criteria. All of the samples and clinical data will be processed and analysed by a double-blind method. The major criteria of PJI (a sinus tract communicating with the joint or two positive cultures of the same organism) are identical among various diagnostic criteria [10–14, 16]. Therefore, we will use the major criteria as the gold standard to divide the enrolled patients into a PJI group and an Aseptic group. Then, we will compare the diagnostic efficiency of the respective minor criteria among the 2018 new definition (before revision and after revision), the MSIS criteria, the ICM criteria and the IDSA (Infectious Diseases Society) criteria (Tables 1, 2, 3, 4 and 5) [10–14, 16]. All patients included in our study will be followed for at least 1 year.

**Table 1 Tab1:** New scoring based definition for periprosthetic joint infection (PJI)

Major criteria (at least one of the following)				Decision
Two positive cultures of the same organism				Infected
Sinus tract with evidence of communication to the joint or visualization of the prosthesis				
Preoperative Diagnosis	Minor criteria		Score	Decision
	Serum	Elevated CRP or D-Dimer	2	≥6 Infected 2–5 Possibly Infected^a^ 0–1 Not Infected
		Elevated ESR	1	
	Synovial	Elevated Synovial WBC or LE	3	
		Positive Alpha-defensin	3	
		Elevated Synovial PMN (%)	2	
		Elevated Synovial CRP	1	
Intraoperative Diagnosis	^a^Inconclusive pre-op score or dry tap		Score	Decision
	Preoperative Score		–	≥6 Infected 4–5 Inconclusive^b^ ≤3 Not Infected
	Positive Histology		3	
	Positive Purulence		3	
	Single Positive Culture		2	

Proceed with caution in: Adverse local tissue reaction, crystal deposition disease, slow growing organisms

^a^For patients with inconclusive minor criteria, operative criteria can also be used to fulfill definition for PJI

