^b^Consider further molecular diagnostics such as next-generation sequencing

**Table 2 Tab2:** Proposed 2018 ICM criteria for PJI (modified version of the 2018 new definition)

Major criteria (at least one of the following)				Decision
Two positive growth of the same organism using standard culture methods				Infected
Sinus tract with evidence of communication to the joint or visualization of the prosthesis				
Minor Criteria	Threshold		Score	Decision
	Acute^b^	Chronic		Combined preoperative and postoperative score: ≥6 Infected 3–5 Inconclusive^a^ <3 Not Infected
Elevated CRP (mg/L)	100	10	2	
or				
D-Dimer (ug/L)	Unknown	860		
Elevated Serum ESR (mm/hr)	No role	30	1	
Elevated Synovial WBC (cells/μL)	10,000	3000	3	
or				
Leukocyte Esterase	++	++		
Or				
Positive Alpha-defensin (signal/cutoff)	1.0	1.0		
Elevated Synovial PMN (%)	90	70	2	
Single Positive Culture			2	
Positive Histology			3	
Positive Intraoperative Purulence^c^			3	

^a^Consider further molecular diagnostics such as Next-Generation Sequencing

^b^These criteria were never validated on acute infections

^c^No role in suspected adverse local issue reaction

**Table 3 Tab3:** Musculoskeletal Infection Society (MSIS) criteria proposed in 2011

Major criteria	
1. There is a sinus tract communicating with the prosthesis	
2. A pathogen is isolated by culture from at least two separate tissue or fluid samples obtained from the affected prosthetic joint	
Minor criteria	
1. Elevated serum erythrocyte sedimentation rate (ESR) and serum C-reactive protein (CRP) concentration	
2. Elevated synovial leukocyte count	
3. Elevated synovial neutrophil percentage (PMN%)	
4. Presence of purulence in the affected joint	
5. Isolation of a microorganism in one culture of periprosthetic tissue or fluid	
6. Greater than five neutrophils per high-power field in five high-power fields observed from histologic analysis of periprosthetic tissue at× 400 magnification.	

PJI exists when one of the major criteria occurs or four of the six minor criteria occur

**Table 4 Tab4:** International Consensus Meeting (ICM) criteria proposed in 2013

Major criteria	
1. Two positive periprosthetic cultures with phenotypically identical organisms	
2. A sinus tract communicating with the joint	
Minor Criteria	
1. Elevated serum C-reactive protein (CRP) and erythrocyte sedimentation rate (ESR)	
2. A single positive culture	
3. Elevated synovial fluid white blood cell (WBC) count or ++ change on leukocyte esterase test strip	

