### Secondary outcomes

The following will be assessed:

Specificity, true positive, true negative, false positive, false negative, positive predictive value and negative predictive value of the new definition (before and after revision).

Sensitivity, specificity, true positive, true negative, false positive, false negative, positive predictive value and negative predictive value of the MSIS criteria.

Sensitivity, specificity, true positive, true negative, false positive, false negative, positive predictive value and negative predictive value of the ICM criteria.

Sensitivity, specificity, true positive, true negative, false positive, false negative, positive predictive value and negative predictive value of the IDSA criteria.

The outcomes above are calculated from the data of patients’ medical record information and laboratory tests. We would like to summarize these outcome data as follows. Patients’ basic information such as demographics, comorbidities and surgery information will be collected first through reviewing patients’ medical records or asking patients themselves. Then we will collect data of serum indicators, synovial indicators and intraoperative indicators of each patient. Serum indicators consist of serum C-reactive protein (CRP), serum D-Dimer, serum interleukin-6 (IL-6) and erythrocyte sedimentation rate (ESR). Synovial indicators consist of synovial white blood cell (WBC), leukocyte esterase (LE), synovial alpha-defensin, synovial polymorphonuclear neutrophil percentage (PMN%) and synovial CRP. Intraoperative indicators consist of histology (pathological data from freezing tissue slices), existence of purulence and microorganism culture. These outcome data will be used to determine whether PJI occurs according to various criteria. Finally, we will acquire result of sensitivity, specificity, true positive, true negative, false positive, false negative, positive predictive value and negative predictive value of five diagnostic criteria of PJI. The concrete methods of data acquisition and processing are clearly introduced in the subsequent ‘Recruitment and intervention’ section.

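### Histology, a reader's neutrophil count, is sent down the unmasked route for objective tests, leaving an uncontrolled risk of test review bias that weighs unequally on the five criteria

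*Protocol article*

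**What the plan says.** The Protocol article has a section on masking, Blind reading of outcomes, which sends the indicators down two routes.

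- **Direct route.** It begins "The results of objective indicators, including demographic characteristics, serum CRP", goes on to include "culture results (tissue or synovial fluid), drug sensitivity, histological analysis", and ends by saying that these results "will be directly recorded by the investigator collecting test results". The people listed as having access to patient information include "the investigator managing synovial fluid samples and the investigator collecting the test results".
- **Masked route.** "The remaining indicators will be first processed and evaluated by an investigator blinded to the details of the patients and samples". The indicators then named are the leukocyte esterase strip and the ELISA measurements of synovial alpha-defensin and synovial CRP. Purulence is openly stated to be judged by surgeons who know the patient.

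Study design and objectives makes a wider claim: "All of the samples and clinical data will be processed and analysed by a double-blind method".

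On what histology is, Table 3 (MSIS) reads "Greater than five neutrophils per high-power field in five high-power fields observed from histologic analysis of periprosthetic tissue", and Secondary outcomes gives the source as "histology (pathological data from freezing tissue slices").

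**The concern.** Histology is part of the index tests. The major criteria (sinus tract, or two cultures of the same organism) are the reference standard. If the person reading the slide knows the reference result or the group, borderline slides can drift toward positive in PJI patients and toward negative in Aseptic patients. This is test review bias, and it would raise sensitivity and specificity together.

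The information that could cause it exists before the tissue is taken. Recruitment and intervention assigns the group at enrolment. It also says that PJI patients are generally aspirated before admission, so culture results are at hand when they attend, while Aseptic patients are not aspirated before surgery.

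The allocation is also uneven. Instrument-read ELISA assays get a masked evaluator, and a visual count does not. Purulence has to be seen by the surgeon, but a slide can be masked by its label. The Discussion concedes that surgeons may select tissue in a way that biases histology. That is a different mechanism from the reading.

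At stake is the comparison of the five criteria, from which the Conclusion intends to name the best method of diagnosis.

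**Working it through.** **Step 1. Weight of histology in each rule (from Tables 1 to 5).**

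| Criterion | Rule | Histology's share |
|---|---|---|
| 2018 new definition (Table 1) | 6 points or more; histology 3, counted only after an inconclusive pre-operative score or a dry tap | 3/6 = 50% |
| Modified 2018 (Table 2) | 6 points or more in the combined score; histology 3 | 3/6 = 50% |
| MSIS (Table 3) | 4 of 6 minor items | 1/4 = 25% |
| ICM 2013 (Table 4) | 3 of 5 minor items | 1/3 = 33% |
| IDSA (Table 5) | acute inflammation is an item by itself | 100% |

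These shares come from the document and need no assumption.

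**Step 2. Formula.** Suppose histology is independent of the other items within a group, and its positivity rate drifts by d. Then the change in the rate of infected calls = d × D, where D is the probability that the other items leave histology decisive (infected with it, not infected without it).

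**Step 3. Assumed marker rates (none is in the document).** Order: serum CRP, D-dimer, ESR, synovial WBC, LE, alpha-defensin, PMN%, synovial CRP, purulence, single culture.

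- PJI, stronger markers: 0.80, 0.75, 0.75, 0.80, 0.70, 0.85, 0.80, 0.80, 0.40, 0.30.
- PJI, weaker markers: 0.60, 0.50, 0.55, 0.50, 0.45, 0.55, 0.50, 0.50, 0.20, 0.30.
- Aseptic: 0.15, 0.25, 0.20, 0.07, 0.07, 0.04, 0.10, 0.10, 0.02, 0.05.

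IDSA is reduced to histology or purulence. All marker combinations are enumerated exactly.

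**Step 4. Two values of D by hand (stronger set).**

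- ICM 2013: histology decides when exactly 2 of the 4 other items are positive. Their rates are CRP and ESR 0.80 × 0.75 = 0.60; culture 0.30; WBC or LE 1 − 0.20 × 0.30 = 0.94; PMN% 0.80. The six pairs sum to 0.00216 + 0.07896 + 0.02016 + 0.02256 + 0.00576 + 0.21056 = 0.340. A 10-point drift gives 0.10 × 0.340 = 3.4 points.
- IDSA: histology decides when there is no purulence, 1 − 0.40 = 0.60. A 10-point drift gives 6.0 points.

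**Step 5. Sensitivity when histology positivity in PJI patients moves from 70% to 80%.**

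| Criterion | Stronger markers | Weaker markers | Change (points) |
|---|---|---|---|
| 2018 new | 0.9987 to 0.9991 | 0.9452 to 0.9573 | 0.04 to 1.2 |
| Modified 2018 | 0.9900 to 0.9932 | 0.9047 to 0.9285 | 0.3 to 2.4 |
| MSIS | 0.5464 to 0.5850 | 0.1946 to 0.2143 | 2.0 to 3.9 |
| ICM 2013 | 0.8220 to 0.8560 | 0.5217 to 0.5617 | 3.4 to 4.0 |
| IDSA | 0.820 to 0.880 | 0.760 to 0.840 | 6 to 8 |

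**Step 6. Specificity when histology positivity in Aseptic patients moves from 10% to 5%.** 2018 new 0.9327 to 0.9460 (1.3 points); modified 2018 0.9436 to 0.9570 (1.3); MSIS less than 0.1; ICM 2013 0.9957 to 0.9971 (0.1); IDSA 0.882 to 0.931 (4.9).

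**Step 7. Scale.** Sample size plans to analyse 60 PJI patients and assumes a sensitivity of 94.9%. The exact 95% interval at 57/60 runs from about 86% to 99%, which is wide beside the shifts for the 2018 versions in step 5.

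**The case against.** The strongest objection is that unmasked reading is inferred. The pathologist is not among the people listed with access to patient information, nor among those who cannot be blinded. Direct recording describes how a finished result is transcribed, not what the slide reader knew, and the design section claims double-blind processing. This stands as a limit on the claim: a reader might infer that the slides are read unmasked, and the document does not say so. It does not remove the point, because the section devoted to masking names histology and assigns it to the route without a masked step. That is a stated allocation, not a detail left to a fuller document.

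A second objection is that a numeric cut-off makes the objective label less unreasonable. That is partly fair. Table 3 does not say that the reader picks the fields, so no weight is put on field selection. Counting cells against a cut-off on a frozen section is still a human reading.

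A third is that the bias might be thought to change which criterion wins. That is not shown. In step 5 the two 2018 versions stay first and second on sensitivity in both assumed sets. The only swap is between ICM 2013 and IDSA in the stronger set, which start at 0.822 and 0.820, so the near-tie comes from the assumed rates. The gaps between criteria move, and in the stronger set the gap of the modified 2018 version over ICM 2013 shrinks (16.8 to 13.7 points). There the drift works against the 2018 versions on sensitivity, not for them.

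It is also fair that equal nominal weight in the two 2018 versions does not mean equal influence, since Table 1 counts histology only at the second stage. The enumeration includes the staging after an inconclusive score.

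**Conclusion.** The point holds as an uncontrolled risk. Histology is placed by name with the directly recorded tests, no masked reading is described, and this falls short of the double-blind claim in Study design and objectives. Any drift in reading would enter the five criteria by unequal amounts, which follows from Tables 1 to 5 alone.

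For the primary outcome, sensitivity of the two 2018 versions, the effect is probably small: 0.04 to 2.4 points for a 10-point drift. The larger effects are on the comparators' sensitivity (2.0 to 4.0 points for MSIS and ICM 2013, 6 to 8 for IDSA) and on specificity (about 1.3 points for the 2018 versions and 4.9 for IDSA, for a 5-point drift). These sizes rest on assumed, independent marker rates, assumed drifts and a simplified IDSA rule.

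The document does not support saying that the pathologist is unmasked, that bias has occurred, or that the ranking would change. This is a cheap improvement worth making before slides are read, because a slide already read with knowledge of the group can be masked again only by re-reading it.

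**What to change.** - In Blind reading of outcomes, move histological analysis from the directly recorded list to the indicators evaluated blind. This brings the section into line with Study design and objectives for this indicator.
- In Recruitment and intervention, state that the three histology samples carry the patient number only.
- State that the pathologist who already reads the samples records the study result at the first reading, without group, sinus tract or culture information. If this is already done, say so.
- Where the reader already knows the clinical details because of the patient's care, flag that reading as unmasked in the data. Relabelling the slide afterwards would not mask that reader.

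The cost is a sentence or two of text, a change of labels and some extra sample handling. The reader and slides stay the same, and no sample-size figure changes.

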### Sample size

Sample size calculations were performed using PASS software version 19.0.2 (licensed by NCSS, LLC). In our retrospective study, the sensitivity and specificity of the new definition were 94.9% (95% confidence interval [CI] 87.9–98.1%) and 95.2% (95% CI 90.3–97.7%), respectively [15]. Based on the results of our calculation, we should analyse the data of 60 patients in the PJI group and 58 patients in the Aseptic group. Therefore, we need to include at least 63 patients in the PJI group and 61 patients in the Aseptic group under the assumption of 5% withdrawal and loss to follow-up. In case some patients are excluded from the study for other clinical reasons, we decided to include at least 70 patients in each group.

### Statistical analysis

The statistical analysis will be carried out with IBM SPSS statistics version 20 (SPSS Inc., Armonk, NY). Descriptive statistics will be determined as numbers (frequencies), medians (lower quartile, upper quartile) and means ± standard deviations. Differences in demographic characteristics will be analysed with the Chi-square test or Student’s t-test. Statistical significance will be defined as a *p* value < 0.05. We will calculate the true positive, true negative, false positive, false negative, positive predictive value and negative predictive value of the various criteria and finally obtain the sensitivity and specificity results.

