### Primary outcome

The diagnostic efficiency (sensitivity) of PJI with the minor criteria of the 2018 new definition (before and after revision).

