**Fig. 2 Fig2:**
[figure not shown]
Management of synovial fluid and test results of leukocyte esterase (LE). The synovial fluid samples acquired preoperatively and intraoperatively are all centrifuged and divided into 3–4 samples. The centrifuged samples will be stored at − 80 C freezer for further study. Synovial fluid samples before centrifugation and after centrifugation are separately used for the test of LE. The results of LE test will be photographed and recorded

During the operation, we will collect three periprosthetic tissue samples from each patient for microorganism culture and three tissue samples for histological analysis. Meanwhile, synovial fluid will be intraoperatively collected and processed as described above. An experienced surgeon will record whether purulence is present in the articular cavity.

The stored synovial fluid of the patients will be numbered, and the details will be recorded by an investigator responsible for managing synovial fluid samples. The number of the synovial fluid sample should be identical to the number of the corresponding patient. Then, the synovial fluid will be delivered to an investigator blinded to the details of the sample who will measure the synovial alpha-defensin and synovial CRP levels by the ELISA (enzyme linked immunosorbent assay) method [19–21].

All of the above data will be delivered to an investigator for statistical analysis. The investigator will only receive the patient number and various indicator values and will determine whether the patient is suffering from PJI based on the test results using different diagnostic criteria. Five kinds of diagnostic criteria are shown in the Tables 1, 2, 3, 4 and 5. The patient meeting one of these criteria will be considered a PJI patient according to this criteria. Using the five diagnostic criteria, the investigator responsible for the statistical analysis will finally determine five diagnoses respectively corresponding to five diagnostic criteria for each patient. Statistical results will be sent to researchers for calculation of the primary and secondary outcomes.

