## Conclusion

The results of this prospective study are expected to strongly support the preceding retrospective study carried out by us. Through the study, we will validate the feasibility of the 2018 new PJI definition (and its modified version) for Chinese patients and determine the optimal method of PJI diagnosis.

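### Five criteria are to be compared on the same patients and an optimal one named, but the stated analysis ends at point estimates and the sample size rests on one criterion's own proportions

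*Protocol article*

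**What the plan says.** The Study design and objectives section says "we will compare the diagnostic efficiency of the respective minor criteria among the 2018 new definition" (before and after revision) and the MSIS, ICM and IDSA criteria. It adds that "all patients serve as their own controls". Under Recruitment and intervention, the investigator responsible for the analysis "will finally determine five diagnoses respectively corresponding to five diagnostic criteria for each patient". The Conclusion, and the conclusion of the Abstract, say the study will "determine the optimal method of PJI diagnosis". The Discussion also promises a comparison of the 2018 definition with its revised version.

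The primary outcome is the sensitivity of the two 2018 versions. Specificity, predictive values and all results for the other three criteria are secondary.

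The Sample size section cites 94.9% sensitivity and 95.2% specificity for the new definition in the retrospective study. From these it concludes that "we should analyse the data of 60 patients in the PJI group and 58 patients in the Aseptic group", raised to 63 and 61 for 5% loss and then to at least 70 per group.

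The Statistical analysis section sets significance at p < 0.05. The only tests it attaches to anything are those in "Differences in demographic characteristics will be analysed with the Chi-square test" or Student's t-test. For the criteria it lists counts and predictive values, to "finally obtain the sensitivity and specificity results".

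**The concern.** Three parts of the article do not fit together. The aim is comparative, the data are paired (five classifications of each patient), and the described analysis contains no contrast between criteria and no interval. The sample size cannot fill the gap, because no comparator rate, target difference, discordance or power enters it.

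If the article is followed as written, the study ends with five sensitivities and five specificities and no measure of uncertainty for the differences between them. Any statement about the optimal method would then rest on raw differences, which at this size may be only a few patients. The article also does not say how sensitivity and specificity are to be weighed together in that statement. The Conclusion expects strong support for the retrospective study, which reported significantly higher sensitivity than MSIS and ICM. Confirming that result requires an analysis of the difference.

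**Working it through.** **Inputs from the protocol article.** Sensitivity 0.949 and specificity 0.952 for the new definition; 60 PJI and 58 Aseptic patients evaluable; at least 70 per group recruited; significance at p < 0.05 (Sample size and Statistical analysis sections).

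**Assumptions, because the article gives no figure.** The test is two-sided. The gap in sensitivity between two criteria is taken as 5, 10 or 15 points. Reverse discordance, meaning PJI patients whom the less sensitive criterion detects and the more sensitive one misses, is taken as 0–2%.

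**Step 1: reproduce 60 and 58.** The width of the exact (Clopper–Pearson) 95% interval for one proportion, with x = np, is Beta⁻¹(0.975; x+1, n−x) − Beta⁻¹(0.025; x, n−x+1).

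- p = 0.949: n = 59 gives 0.1310; n = 60 gives 0.1298 (0.859 to 0.989).
- p = 0.952: n = 57 gives 0.1307; n = 58 gives 0.1294 (0.861 to 0.991).

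So 60 and 58 are the smallest sizes with a full width of at most 0.13. That width is back-solved, not stated. Other one-proportion routes come close. A one-sided one-sample test against 0.85 at 80% power gives 61 and 57 (normal) or 59 and 59 (exact). A two-sided test against 0.83 at 80% power gives 60 and 57 (normal). Each of these routes sizes a single proportion, and the section states no input for a comparison. At 70 per group the exact widths fall to 0.119 and 0.116.

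**Step 2: the smallest significant paired difference.** If k discordant patients all fall one way, the exact two-sided McNemar p is 2 × 0.5^k. Five give 0.0625 and six give 0.031. At least six net patients are therefore needed: 6/60 = 10 points, or 6/70 = 8.6 points.

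**Step 3: power of the exact McNemar test for sensitivity.** The number of discordant pairs is binomial (n, b + c). Given m discordant pairs, the number favouring the better criterion is binomial (m, b/(b + c)), where b − c is the gap and c the reverse discordance. Power is the summed probability of outcomes with p ≤ 0.05. With c = 0 it reduces to P(X ≥ 6) for X binomial (n, gap), which is 0.079 for n = 60 and a gap of 0.05, and 0.563 for a gap of 0.10.

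| True gap in sensitivity | n = 60 | n = 70 |
|---|---|---|
| 5 points | 8–10% | 14% |
| 10 points | 43–56% | 52–71% |
| 15 points | 74–90% | 82–96% |

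The ranges cover c = 0 to 0.02. They are for a single contrast; a multiplicity correction would lower them.

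**Step 4: precision of a paired difference.** For a gap near zero and total discordance d, the Wald half-width is about 1.96 × √(d/n). At n = 60, d = 0.04 gives 0.051 and d = 0.09 gives 0.076. Two criteria that truly perform alike would be separated only to within about ±5 to ±7.5 points.

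**The case against.** The strongest reply is that a condensed article commonly leaves the paired test and the interval method to an analysis plan, which is not shown. On this view nothing stated is wrong: no unpaired test is prescribed for the criteria, pairing is acknowledged, and the same group reported intervals and a significance statement for its retrospective study. The size also suits the primary outcome, which is the sensitivity of the 2018 versions with no contrast. The listed objectives speak of validating feasibility, not of ranking.

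Part of this stands. A missing McNemar test alone would be no finding, and sizing on one proportion is coherent for estimating one proportion. But the article does describe how the criteria are analysed, and that description stops short of the comparison it promises. The sizing basis and the claim of an optimal method are fixed in the article, and an analysis plan would not change what 60 to 70 patients can resolve.

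Some stronger readings are tempting, but the documents do not support them:

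- A reader might infer that the criterion with the highest point estimate will be declared optimal whatever its specificity. The article contains no such rule, and it reports specificity and predictive values for all five criteria.
- A reader might infer that a looser criterion must gain sensitivity and lose specificity. For nested rules sensitivity cannot fall and specificity cannot rise, but neither need change. These criteria also differ in items, weights and cut-offs.
- A reader might infer that the two 2018 versions cannot be told apart. Tables 1 and 2 score synovial CRP, alpha-defensin and the intraoperative items differently, and their discordance is unknown. A large difference could show.
- A reader might take the 0.13 width as the planning basis. It fits exactly, but it is inferred.

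**Conclusion.** The point holds in this form: the promised comparison and the optimal-method claim go beyond both the stated analysis and the stated sizing basis. At 60 to 70 PJI patients a 5-point gap in sensitivity would usually be missed (power 8–14%), and a 10-point gap would be found in roughly half to 70% of studies (43–71%). A gap of about 15 points could be shown (74–96%), so the ranking lacks support for small and moderate gaps, not for every possible gap. These figures assume a two-sided exact McNemar test at 0.05, one contrast and 0–2% reverse discordance. The article gives no comparator sensitivities, so the true gaps are unknown. The conclusion that the size was set without a comparison does not depend on which one-proportion method was used. The point should be corrected, and it can be dealt with by changes of wording.

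**What to change.** - **Statistical analysis section:** state that each 2018 version will be compared with each of MSIS, ICM and IDSA, and the two versions with each other, by the paired difference in sensitivity (PJI group) and in specificity (Aseptic group), with a 95% confidence interval and an exact McNemar test. That is 2 × 3 + 1 = 7 contrasts on two measures, or 14 tests, so add a multiplicity rule or label the contrasts exploratory. Give exact 95% intervals for each criterion's sensitivity and specificity.
- **Interpretation:** say that sensitivity and specificity will be judged together before one criterion is called better than another. Making specificity co-primary is not required.
- **Abstract and Conclusion:** limit the optimal-method wording to what the paired intervals support. Otherwise say that the study estimates the accuracy of each criterion.
- **Sample size section:** state the actual PASS inputs behind 60 and 58 (method, and width or null value, confidence level or power), and say that the size was not set for comparing criteria.

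The cost is a little more analysis and a softer conclusion. No more patients are needed, provided the claim is limited in this way.
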